## Abstract

**Background:**

It is estimated that 39,000 Australians die from malignant disease yearly. Of these, 60% to 88% of advanced cancer patients suffer xerostomia, the subjective feeling of mouth dryness. Xerostomia has significant physical, social and psychological consequences which compromise function and quality of life. Pilocarpine is one treatment for xerostomia. Most studies have shown some variation in individual response to pilocarpine, in terms of dose used, and timing and extent of response.

We will determine a population estimate of the efficacy of pilocarpine drops (6 mg) three times daily compared to placebo in relieving dry mouth in palliative care (PC) patients. A secondary aim is to assess individual patients’ response to pilocarpine and provide reports detailing individual response to patients and their treating clinician.

**Methods/Design:**

Aggregated n-of-1 trials (3 cycle, double blind, placebo-controlled crossover trials using standardized measures of effect). Individual trials will identify which patients respond to the medication. To produce a population estimate of a treatment effect, the results of all cycles will be aggregated.

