### Primary and secondary endpoints

#### Primary outcome

Symptomatic improvement will be measured by NRS score for average dry mouth (answer to the question – how dry was your mouth on average over the last 24 hours?). A clinically significant response to pilocarpine will be defined as a ≥2 point improvement in xerostomia NRS score compared to placebo. This is in view of previous work, where a 20% (2 cm) improvement or more against the baseline score was considered to be a positive improvement [21,22]. NRS data will be collected on days 2 and 3 of each cycle pair to allow wash-out during day 1.

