(i) Oral health related quality of life will be measured by Oral Health Impact Profile (OHIP) [29], a short 14 item questionnaire that has been validated in a population with xerostomia, although not in cancer or PC.

(a) *Patient Global Impression of Change (PGIC)*:

Is a standardised, validated questionnaire that addresses change in activity limitation, emotions, symptoms and overall quality of life [30].

2. *Timing and content of assessments*

3. *Individual patient reports*

At the end of the trial, the order of medications will be unmasked, and compared with the patient’s observations. Repeated results in the same direction favouring the treatment will be reported in terms of a probability that the observed result is true. The clinical importance of the result will be described by comparing it to a predetermined clinically important change. A clinically significant response to pilocarpine or placebo will be defined as a ≥2 point improvement in xerostomia NRS score compared to baseline, in view of previous work, where a 20% (2 cm) improvement or more against the baseline NRS score was considered to be a positive improvement [21,22]. A report on the patient’s response to pilocarpine will be forwarded to the patient’s doctor so a decision on further treatment can be made.

Palliative care clinicians who recruit participants will most likely also receive the post-treatment report. This potentially may unblind the clinician during the course of the trial in relation to the possible effectiveness of pilocarpine, and particular characteristics of responders. Ideally the clinician recruiting to the study will be a different to the one receiving the results and treating the patient. Collecting data from patients independent of clinicians minimises observer bias.

4. *Withdrawals*

Patients who discontinue the study for whatever reason will be able to resume if their condition can be re-stabilised for at least 1 week. Patients who cannot resume the trial will have their completed cycle results added to the trial dataset for later calculation of the population effect of pilocarpine. If a patient’s withdrawal from the study could be attributed to the intervention, their data will contribute to the analysis under intention to treat principles.

**Table 1 T1:** Schedule of assessments

**Measure**	**Baseline**	**Daily**	**Every 3 days**	**End of 6 day cycle**	**End of trial**
Demographics	x				
Vital Signs	x				
Routine blood test	x				
AKPS	x				x^1^

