### Analysis

#### Sample size calculations

Power calculations were based on the primary outcome variable, the NRS score, and a pooled mean (standard deviation) baseline score across groups of 3.250 (2.975) from Davies et al., 1998 [15] (with correction, 1999). Thomson and Williams’ 2000 [31] article on testing the xerostomia inventory was used to estimate patients’ ICC (intra class correlation). In their table IV, Thomson and Williams give a correlation between standard-question responses that range from 0.20 to 0.76, so we assumed a value of 0.3 (approximately the median). From Bland 2000 [32] [page 204], recognising that r ≈ ICC = *s*_
*b*
_^2^/ (*s*_
*b*
_^2^ + *s*_
*w*
_^2^) where *s*_
*b*
_^2^ is the between subject variance and *s*_
*w*
_^2^ is the within subject variance, we can thus determine that *s*_
*w*
_^2^ ≈ 4.752. Of the 70 palliative care patients randomized by Davies et al. [15], 36 (51%) completed phase I (14 days in length) and 26 (37%) completed phase II (21 days in length after phase I completion). Based on this attrition rate, but recognizing the shorter duration of our study, we expect that approximately 60% of our patients will complete cycle I, 50% will complete cycle II, and 45% will complete cycle III.

If we assume no period effect or treatment × time interaction, then simulations of size N = 10,000 in Stata (Statacorp, College Station, TX) programmed to model the repeated measures design, attrition rates, and *s*_
*b*
_^2^ and *s*_
*w*
_^2^ variances above, then n = 70 patients need to be recruited to detect a 2 cm change in NRS scores between treatments with 80% power at the 5% level of significance. With n = 70, we expect 31 patients will complete all 3 cycles, 4 will complete cycles I and II, 7 will complete cycle I, and 28 will fail to complete any cycles. In contrast, a conventional RCT with similar attrition would require 120 patients.

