#### Data analysis

Data preparation and descriptive reporting will follow that recommended by the CONSORT statement [25].

For each cycle, data from day 1 will be discarded to allow for a wash-out period, and data from days 2 and 3 data will be analysed. All patients with at least one completed treatment cycle will be included in analyses. An effect size will then be calculated between active medication cycles and placebo, thus providing a population measure of effect commensurate with an RCT.

Both individual and population treatment differences will be estimated using hierarchical Bayesian methods and employing noninformative priors using the methods described in Zucker et al. [33], and Schluter and Ware [34]. The likelihood distributions for each model will be assessed for violations and data transformations undertaken, where necessary. Conventional burn-in periods, model convergence and stability diagnostics, and residual checks will be employed [35]. WinBUGS [35] will be used for the Bayesian analysis.

To describe participants’ overall response, three types of Bayesian results will be presented: (i) the mean of the posterior distribution of the mean difference between placebo and stimulant scores, which gives the best estimate of the overall effect size difference between treatments; (ii) the associated 95% credible region, which give intervals of uncertainty (in this case the 2.5 and 97.5 percentile) of the posterior distributions used in (i); and (iii) the posterior probability of the mean difference that stimulant scores were better than placebo scores, which describes the likelihood that the patients will favour the active treatment in future cycles [34]. A patient will be defined to be a ‘responder’ when these estimated values exceed predefined threshold values [34].

Important confounding variables, such as anti-cholinergic load and cause of xerostomia (eg prior radiotherapy), will in included in adjusted analyses and report treatment effects (or success differences) over the various variable stratifications and combinations, following the method advocated by Zucker and colleagues [33].

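### The plan promises to identify individual responders, but a 2-point cut on one to three cycles carries sizeable labelling error, and the planned posterior probability does not refer to that cut

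*Protocol article*

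**What the plan says.** The abstract (Methods/Design) states: "Individual trials will identify which patients respond to the medication". Assessing individual response, and reporting it to the patient and clinician, is the stated secondary aim.

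Three places say what counts as a response, and they differ:

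- Primary outcome: "A clinically significant response to pilocarpine will be defined as a ≥2 point improvement in xerostomia NRS score compared to placebo".
- Patient assessment, individual patient reports: "A clinically significant response to pilocarpine or placebo will be defined as a ≥2 point improvement in xerostomia NRS score compared to baseline". The same section adds: "Repeated results in the same direction favouring the treatment will be reported in terms of a probability that the observed result is true". The report goes to the patient's doctor to inform the decision on further treatment.
- Data analysis: "Both individual and population treatment differences will be estimated using hierarchical Bayesian methods and employing noninformative priors". It lists a posterior mean difference, a 95% credible region and a posterior probability that active is better than placebo. It then says: "A patient will be defined to be a ‘responder’ when these estimated values exceed predefined threshold values".

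On the amount of data per patient, the sample-size section expects that "approximately 60% of our patients will complete cycle I, 50% will complete cycle II, and 45% will complete cycle III". Everyone with at least one completed cycle is analysed.

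**The concern.** Two of the three definitions apply a fixed 2-point cut to a point estimate and say nothing of its error. The third carries uncertainty, but its stated probability is of any benefit over placebo, not of a benefit of 2 points. Power is given only for the population difference. If one patient's estimate is about as imprecise as the threshold is large, a label from the bare cut will often be wrong. Some patients with no benefit would be reported as responders and some with a clear benefit would be missed, in a report meant to guide treatment. The baseline version adds a further problem: change from baseline includes whatever change also occurs on placebo, so a patient can meet it on both treatments.

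**Working it through.** **Inputs.** Within-patient variance 4.752 and the 31/4/7 split of patients completing three, two and one cycles (sample size calculations); at most three cycles (aggregated n-of-1 trial design); days 2 and 3 of each period analysed (data analysis); threshold 2 points.

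**The plan's own variance.** SD 2.975 gives a total variance of 2.975² = 8.851. With ICC 0.3 the within-patient part is 0.7 × 8.851 = 6.195, not 4.752. The printed value implies an ICC of 1 − 4.752/8.851 = 0.46. I use 4.752 because it is the stated figure and the more favourable one.

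**Standard error of one patient's mean difference over k cycles:** SE = √(2 × 4.752 × f / k). The plan does not say whether 4.752 refers to one day or to a period mean. I therefore take f = 0.5 (one-day variance, two independent days averaged) to f = 1 (no gain from the second day).

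**Error rates of a raw 2-point cut,** with normal errors. False label at zero effect = P(Z > 2/SE). Miss at a true 3 points = P(Z < −1/SE).

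| Cycles | SE | False label, true effect 0 | Missed, true effect 3 |
|---|---|---|---|
| 3 | 1.26 to 1.78 | 6% to 13% | 21% to 29% |
| 2 | 1.54 to 2.18 | 10% to 18% | 26% to 32% |
| 1 | 2.18 to 3.08 | 18% to 26% | 32% to 37% |

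With 6.195 the three-cycle figures become SE 1.44 to 2.03, 8% to 16% false labels and 24% to 31% missed. None of these rates needs an assumption about how true effects are distributed.

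**Why the planned probability does not close the gap.** Take a patient with an observed difference of 2.5 after three cycles and a flat prior. The probability that active is better than placebo is Φ(2.5/1.78) to Φ(2.5/1.26), or 92% to 98%. The probability that the difference is at least 2 is Φ(0.5/1.78) to Φ(0.5/1.26), or 61% to 65%. The report would look firm on the first and is far from firm on the second.

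**Responder share.** This needs a mean and SD of true effects, which the protocol does not give, so the values below are assumptions. They use the 31/4/7 mix, with f from 0.5 to 1. The shrunken rule cuts the patient's posterior mean at 2.

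| Assumed mean, SD | True share ≥2 | Raw cut labels | Shrunken cut labels | Mislabelled, raw |
|---|---|---|---|---|
| 1, 1 | 16% | 28% to 33% | 2% to 4% | 24% to 29% |
| 1, 2 | 31% | 34% to 36% | 24% to 27% | 18% to 23% |
| 2, 1 | 50% | 50% | 50% | 30% to 35% |
| 2.5, 1 | 69% | 59% to 61% | 81% to 87% | 28% to 33% |

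The counted share can be too high, too low or right. Mislabelling of individuals persists even when the share is right.

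**The case against.** The strongest reply is that the data-analysis section does not use a raw cut. It fits a hierarchical model, gives a credible region and a posterior probability, and defines a responder "when these estimated values exceed predefined threshold values". Those thresholds may well be in the full protocol or analysis plan, so their absence from the article is not a fault. The individual report also promises a probability, and its wording about repeated results hardly fits a single cycle. Requiring all three cycles to favour active as well lowers the zero-effect false-label rate from 6-13% to about 4-8%. The secondary aim is to assess response, not to classify without error, and no counted responder share is declared as an endpoint.

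Most of this stands, and it limits the point. It would be wrong to say that the plan makes no allowance for error anywhere. A reader might also infer that the trial will inflate its responder share, perhaps to nearly double. That holds for a raw cut near a mean of 1 and SD of 1. The ratio is 1 if the mean equals the 2 points used for power, and the error reverses under shrinkage in the same example. The documents fix neither the distribution nor the rule, so they do not support a direction.

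The reply does not remove three things. The bare 2-point definitions are in the text, with two comparators. The stated posterior probability is not of a 2-point difference. And the individual-report section accepts that a clinician may learn results while the trial is still running, which implies that at least some reports precede the full hierarchical fit.

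**Conclusion.** The point holds in a limited form. On the stated variance, the precision of one patient's difference does not support the promise to identify responders. A raw 2-point cut gives 6-13% false labels and 21-29% misses after three cycles, and 18-26% and 32-37% after one, at true effects of 0 and 3 points respectively. Shrinkage changes the pattern of errors but does not make labels reliable: at mean 1 and SD 1, a posterior-mean cut at 2 finds only 6-18% of true responders. By the plan's own forecast, 7 of the 42 patients with data would have one cycle only.

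The figures assume normal, independent errors between periods, ignore the bounded 0-10 scale, and take 4.752 at face value. The population estimate is not affected. The matter is worth correcting because the report is meant to inform treatment and the remedy is close to free.

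**What to change.** 1. Reconcile the primary-outcome, individual-report and data-analysis sections to one responder definition, based on the patient's own active-versus-placebo difference.
2. In each report give the posterior probability that this difference is at least 2 points, with its 95% credible interval, and state which model fit supplies it when the report goes out before the trial ends.
3. Prespecify cut-offs with an inconclusive category between them. Values such as 0.80 and 0.20, or a minimum number of completed cycles for a label, are examples only.
4. Take any responder share from the model's posterior, not from a count of labels.
5. Reword the abstract so that individual trials estimate each patient's response and its uncertainty.

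The cost is wording plus quantities that the planned Bayesian output already yields; no new data are needed. The downside is that many reports will be inconclusive. With a flat prior and 0.80/0.20, the inconclusive band is 2 ± 0.84 × SE. That is observed differences of about 0.9 to 3.1 (SE 1.26) or 0.5 to 3.5 (SE 1.78) after three cycles, and about 0.2 to 3.8 (SE 2.18) or −0.6 to 4.6 (SE 3.08) after one.

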**Discussion:**

Managing dry mouth with treatment supported by the best possible evidence will improve functional status of patients, and improve quality of life for patients and carers. Using n-of-1 trials will accelerate the rate of accumulation of high-grade evidence to support clinical therapies used in PC.

**Trial registration:**

Australia and New Zealand Clinical Trial Registry Number: 12610000840088.

## Background

It is estimated that 39,000 Australians die from malignant disease yearly [1]. Of these, 60 to 88% of advanced cancer patients suffer xerostomia [2], the subjective feeling of mouth dryness. Medications, particularly those with anti-cholinergic side effects such as opioids [3], are the most common cause of xerostomia. Other cases are seen in patients receiving radiotherapy for malignant tumours in the head and neck region as treatment may include salivary glands in their fields causing hypofunction. Patients with reduced salivary flow are at increased risk for dental caries, mucosal breakdown, oral fungal infections, swallowing problems, and diminished or altered taste [4] with secondary symptoms of difficulty in chewing, swallowing and speaking. These symptoms may cause nutritional deficiencies and difficulties in communication and sleeping, leading to overall decline in quality of life [5,6]. Dry mouth symptoms tend to increase towards the end of life [7].

### Pilocarpine

Pilocarpine is a parasympathomimetic agent with predominantly muscarinic activity. Oral pilocarpine formulations are more economical and can be used in lower doses than tablets with reduction in some types of adverse effects [8]. Pilocarpine is very soluble and stable in water solution and the effect lasts for up to 3 hours.

### Efficacy of pilocarpine in reducing xerostomia?

There have been several studies describing symptomatic improvement of dry mouth using pilocarpine in patients with residual salivary function in Sjogren’s syndrome, patients who have received radiotherapy to the head and neck, graft versus host disease, total body irradiation and opioid-induced xerostomia [9-14].

A Cochrane systematic review of pilocarpine for salivary gland dysfunction due to radiotherapy in 2007 [15] suggested that pilocarpine was more effective than placebo, and at least as effective as artificial saliva in those participants that responded (125 (42%) to 151 (51%) from 298 patients). The side effect rate was high (usually the result of generalized parasympathomimetic stimulation) and side effects were the main reason for withdrawal (six to 15% of patients taking 5 mg three times a day). The only study in PC patients, an unblinded single cross-over study, showed that pilocarpine tablets 5 mg tds were more effective than artificial saliva, although they produced more side effects [16].

### N-of-1 trials

The need to improve the evidence base on which PC is based is widely acknowledged [17]. We have previously proposed that n-of-1 trials may provide a mechanism for doing this [18]. N-of-1 trials are multiple-cycle, double blind, placebo-controlled crossover trials using standardized measures of effect (see Figure 1). They provide the strongest evidence possible about the efficacy of a treatment in an individual patient [19]. There are necessary conditions for n-of-1 trials to be conducted, namely: (i) the drug to be tested has a short half-life; (ii) there is no residual impact on the target symptom after excretion; (iii) there is variation in individual response; and (iv) the drug is being used to treat an important and recurrent symptom that has a negative impact on quality of life (QoL). Pilocarpine is a drug ideal for n-of-1 trials: its short half-life allows rapid onset and offset of action; there is variability in response, and it does not change the underlying pathology.

**Figure 1 F1:**
[figure not shown]
**Example of n-of-1 design schema**^
**1**
^**.**

N-of-1 trials are usually used for testing the effectiveness of medicines in individual patients. However, the results of many n-of-1 trials can be combined to determine the effect of a therapy for a population, thus allowing rapid accumulation of strong evidence on treatment effects in patients with advanced life-limiting illness previously very difficult to gather.

## Methods/Design

This study aims to determine a population estimate of the efficacy of pilocarpine drops (6 mg) three times daily compared to placebo in relieving dry mouth in palliative care (PC) patients. A secondary aim is to assess individual patients’ response to pilocarpine and provide reports detailing individual response to patients and their treating clinician.

### Aggregated n-of-1 trial design

This will be an n-of-1 trial with 3 pairs (cycles) of treatment periods comparing active drug to placebo. As pilocarpine has a short half life (0.76 hours for 5 mg tabs), the clinical effect is rapidly evident. Therefore, an appropriate duration of each treatment period is 3 days (thus each treatment pair (or cycle) is 6 days), making a total of 18 days for patients who complete the full trial. The order of drugs in each cycle will be determined by random allocation, blinded to both clinician and patient. Patients who do not complete the full trial will still contribute completed cycles to the final analysis. To produce a population estimate of a treatment effect, the results of all patient cycles will be aggregated [18].

### Setting

Inpatients and outpatients who are eligible will be recruited from 7 hospitals in Queensland and New South Wales, Australia: Ipswich Hospital, Royal Brisbane and Women’s Hospitals, Mater Health Services, St Vincent’s Hospital, Wynnum and Redcliffe Hospitals in Queensland, and in NSW, Calvary Mater Hospital, Newcastle. Ethics approval has been provided by The University of Queensland (UQ) and each site’s institutional ethics committee.

### Participants

a) Inclusion criteria:

1. Patients aged ≥18 years with malignant disease;

1. a clinical diagnosis of chronic dry mouth that has been present for at least 2 weeks with no likelihood of resolution during the trial period

1. a numerical rating scale (NRS) score of ≥3 on a 11-point xerostomia scale;

1. no known allergy or sensitivity to pilocarpine;

1. ability to give fully informed written consent and complete all trial requirements.

b) Exclusion criteria:

1. no plan to change any medication with the potential to cause dry mouth within the trial period. (Patients already on pilocarpine are eligible but must stop this 1 week before trial commencement);

1. no intervention e.g. radiotherapy, chemotherapy, surgery that might alter dry mouth symptoms during the 2 weeks prior to the study period or plans to undergo such therapy during the study period;

1. ocular problems contraindicating the use of parasympathetic agents (eg irido-cyclitis, increased intra-ocular pressure);

1. other comorbidity where there is a risk of worsening co-existing medical problems during the trial period and/or active treatment is contemplated (e.g. severe or uncontrolled asthma or pulmonary disease, uncontrolled hypo-or hypertension, hyperthyroidism, uncontrolled seizures or cardiac arrythmias, (especially bradycardias) and Parkinson's disease);

1. a poor understanding of written or spoken English that would preclude completion of all trial requirements;

1. an active oral infection (e.g. candidiasis, herpetic infections, mucositis, mouth ulcers).

